# Effects of β-hydroxy-β-methylbutyrate (HMB) supplementation in addition to multicomponent exercise in adults older than 70 years living in nursing homes, a cluster randomized placebo-controlled trial: the HEAL study protocol

**DOI:** 10.1186/s12877-019-1200-5

**Published:** 2019-07-05

**Keywords:** Healthy ageing, Physical activity, Physical fitness, Falls, Dynapenia

## Abstract

**Background:**

Evidence supports the fact that multicomponent exercise and HMB supplementation are, separately, effective in improving older adult’s health and palliate functional metabolic diseases in older people. However, the true effect of HMB supplementation combined with a tailored exercise program in frail older adults is still unknown. Thus, the aim of the HEAL (HMB + Exercise = Adults Living longer) study is to assess the effects of the combination of a daily multicomponent exercise and resistance training (VIVIFRAIL program) intervention in addition to HMB supplementation on older adults’ health.

**Methods/design:**

A 24-week cluster randomized, double-blind, placebo-controlled study will be conducted on 104 adults ≥70 years. Nursing homes will be randomized to either of four groups: Ex-HMB (exercise intervention with HMB), Ex-Plac (exercise intervention with placebo), NoEx-HMB (no exercise intervention with HMB), and Controls (No exercise and no HMB). Intervention groups which include exercise will complete the individualized multicomponent (strength, balance and cardiovascular exercises) training program VIVIFRAIL. Intervention groups which include HMB supplementation will receive a 3 g/daily dose of free acid HMB in powder form. The primary outcome measure is the functional capacity. Secondary outcome measures are muscle strength and power, frailty and fall risk, body composition, biochemical analyses and cardiometabolic risk factor, disability and comorbidity, cognitive function and depression.

**Discussion:**

The findings of the HEAL study will help professionals from public health systems to identify cost-effective and innovative actions to improve older people’s health and quality of life, and endorse exercise practice in older adults and people living in nursing homes.

**Trial registration:**

NCT03827499; Date of registration: 01/02/2019.

## Background

To date, people are living more years than ever before in history and the world’s aging is rising at a staggering rate [1]. Thus, strategies focused on health maintenance for aging people through exercise and proper nutrition are required to contribute to lifelong wellbeing and prevent ageing diseases and chronic illness. Frailty, sarcopenia, dynapenia and sarcopenic obesity states are the main metabolic complications in older people and represent a major public health challenge [2–4]. A recent estimation from the Eurostat online database (28 European countries) suggests increments from 60 to 70% of individuals with sarcopenia in 2045 affecting 12.9 to 22.3% of people over 65 years old [5]. These diseases are caused by a degenerative loss of muscle mass (muscle wasting), strength and mobility. The combination of exercise with protein dietary supplementation is proven to be highly effective to increase muscle mass and strength in older adults [6–8].

Evidence states that exercise in older people is a main component in frailty prevention (increases strength and decreases falls incidence) and functional capacity preservation (increases mobility and autonomy) [8–10]. In turn, weak elders have greater risk of disability, hospitalization, morbidity and death [3, 11]. In addition to a better physical condition, exercise has a clear impact on psychological well-being in older people [12]. Although much remains to be done, the possibility of physical exercise as the new medication for the twenty-first century is truly inspiring. The first step of this revolution is that the question is turning from “may I prescribe physical activity for older people?” to “what kind of exercise must I prescribe?” [13]. Reducing sedentary behaviours and promoting exercise training in older adults living in nursing homes stands as a main global challenge [14, 15].

Very recently, the ERAMUS+ co-funding VIVIFRAIL project (http://www.vivifrail.com) has developed a multicomponent exercise program (strength, balance and cardiovascular exercises), carefully adapted, for improving functional capacity for older people above 70 years [16]. The program includes a practical guide for testing and prescribing the physical training according to each specific condition (serious, moderate, slight or no limitation, and with or without risk of falling). Furthermore, the VIVIFRAIL App allows individuals’ monitoring and provides clear instructions to effectively complete the program within the everyday environment. Now that long-term exercise interventions in older adults are more possible than ever [17], what is now required is to examine the effectiveness of this program on relevant health and functional outcomes for older adults and nursing homes residents [15].

The β-hydroxy-β-methylbutyrate (HMB) dietary is a bioactive metabolite formed from the decomposition of leucine, an essential branched-chain amino acid. The importance of leucine has anti-catabolic properties and plays an important role in protein metabolism, glucose homeostasis, insulin action and recovery from exercise [18–20]. A dose of 3 g of HMB dietary supplementation provides 60 g of leucine, which otherwise would imply 600 g of high biological value protein [21]. The HMB supplementation is affordable (around 50€/kg) and its consumption is safe with no adverse effects [22, 23]. In older adults > 60 years old, HMB is demonstrated to have anti-catabolic effect, enhance protein synthesis, attenuate proteolysis, increase muscle mass and decrease muscle damage [24–26]. Despite the fact that HMB efficacy varies [25], a meta-analysis concluded that HMB supplements contribute to the preservation of muscle mass in old age [27]. Based on these findings, the supplementation of HMB appears to be an effective strategy to prevent metabolic and physical complications in ageing (frailty, dynapenia, sarcopenia and sarcopenic obesity) and preserve health, functional capacity and strength in older people.

A recent investigation [28] reported for the first time a significant reduction of 50% in whole body plasma concentration of HMB and reductions of 25% on the conversion of leucine to HMB in older adults (~ 65 y-old). At the moment, there is limited understanding why this happens, but it seems clear than reductions in HMB conversion are associated with age [29]. These decrements on high quality protein synthesis importantly accounted for a decline in muscle weakness in older people [30]. Hence, the possibility of palliating muscle and functional losses in the ageing by HMB supplementation is truly inspiring and encourages further studies [26, 27].

To date, only five Randomized Control Trial (RCT) studies have examined the effectiveness of exercise training combined with HMB dietary supplementation in older adults > 60 years old [31–35]. Whereas it seems clear that HMB supplements contribute to the preservation of muscle mass in old age, contradictory evidence on its effects on strength increments [31–34] and functional performance [33–35] in older adults exists. These equivocal outcomes may be attributed to the protocols applied, with discrepancies in the training volume (number of sessions, time per session, number of reps), intensity (load monitoring and progression) and exercises. Besides, sample sizes explored are reduced (*n* < 32) and only one RCT [32] conducted an exercise intervention > 8 weeks. Consequently, there is a need for longer and larger studies to fully determine the potential effects of HMB supplementation on physical performance, translating to a functional benefit [34]. In this sense, the HEAL (HMB + Exercise = Adults Living longer) study will be the first RCT conducting a specific, individualized, multicomponent exercise intervention for the older adult population such as the VIVIFRAIL [16]. Because this evidence-based program has been proven as effective and safe in adults aged 65 years or over [17], it represents an excellent opportunity to determine the true effects of HMB supplementation in enhancing training performance. Furthermore, the promising results of HMB supplementation to mitigate age-related cognitive deficits [36, 37] and the lack of studies exploring its impact on people with very limited or no mobility [25, 38] encourage adopting this strategy in vulnerable people such as older nursing homes patients. Therefore, the aim of the HEAL study is to assess the effects of the combination of a daily multicomponent exercise and resistance training (VIVIFRAIL program) in addition to HMB supplementation on older adults’ health.

## Methods/design

### Study design and settings

This is a cluster randomized, placebo-controlled study with four parallel groups. The study has been designed to determine the efficacy of HMB supplementation in addition to 24-weeks of multicomponent exercise and resistance training (the VIVIFRAIL program) in adults ≥70 years. Flowchart of the trial is shown in Fig. 1. Enrollment, intervention allocation, follow-up, and data analysis will be conducted according to the SPIRIT (Standard Protocol Items: Recommendations for Interventional Trials) statement [39, 40].

**Fig. 1 Fig1:**
[figure not shown]
Flowchart of the trial

### Eligibility criteria

Inclusion criteria for enrollment will be: men and women aged ≥70 years, be able to follow an active physical rehabilitation program and voluntary participation. Enrollment of cognitively impaired older adults will require proxy permission (family member or caregiver) [41]. All potential participants will provide a medical history and undergo a medical examination to identify cardiovascular or metabolic conditions that would exclude participation (for full list, see Table 1).

**Table 1 Tab1:** Exclusion criteria for the HEAL study

Exclusion criteria	
- Acute heart attack (recent 3–6 months) or unstable angina - Uncontrolled atrial or ventricular arrhythmias - Aortic dissecting aneurysm - Severe aortic stenosis - Acute endocarditis / pericarditis - Uncontrolled high blood pressure (> 180/100 mmHg) - Acute thromboembolism - Acute or severe heart failure - Acute or severe respiratory failure - Uncontrolled postural hypotension - Uncontrolled acute decompensated diabetes mellitus or low blood sugar - A recent fracture in the last month. - Coincident participation in any intervention trial - HMB contraindication, intolerance, or allergy - Have regularly performed exercise (> 20 min > 3 days/week) in the last 3 months - Malignant diseases (exceptions: basal or squamous-cell skin carcinoma or carcinoma in situ of the uterine cervix) - Revascularization within 1 year - Severe loss of vision, hearing, or communicative ability - Conditions preventing cooperation	

### Sample size

The required sample size will be determined on the basis on the functional capacity, using the Short Physical Performance Battery (SPPB) [42]. According to previous research on subjects with similar characteristics [17], a clinically relevant change is about 1.5 ± 1.0 points increments after 12-weeks. Differences of 2 point in total SPBB with a standard deviation of 3 points with a power of 80% and α of 0.05 can be estimated with 20 participants using the R software (v. 3.2.1) and the package *samplesize*. Assuming a maximum loss of follow-up of 30%, we will recruit 26 adults ≥70 years per group (*n* = 104). Similar interventions had an adherence rate of 75%, and a mean attendance of 80% to the sessions [17]. Therefore, the current estimation is realistic and affordable.

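### The stated 80% power with 20 participants does not apply to the effect of HMB on top of exercise: the benchmark is an exercise-programme change and no HMB increment is justified

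*Protocol article*

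**What the plan says.** Study design and settings gives the purpose as to "determine the efficacy of HMB supplementation in addition to 24-weeks of multicomponent exercise and resistance training", and the Discussion repeats this. The Abstract and the end of the Background word the aim more loosely, for example to "assess the effects of the combination of a daily multicomponent exercise and resistance training (VIVIFRAIL program) in addition to HMB supplementation".

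The design is a "placebo-controlled study with four parallel groups": Ex-HMB, Ex-Plac, NoEx-HMB and Control. According to Dietary supplementation, both Ex-Plac and Control receive stevioside, so the arms cross exercise (yes/no) with HMB (yes/no).

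Sample size cites reference 17 for "a clinically relevant change is about 1.5 ± 1.0 points increments after 12-weeks". The Background cites the same reference for the exercise programme: "this evidence-based program has been proven as effective and safe in adults aged 65 years or over [17". The calculation then uses neither 1.5 nor 1.0: "Differences of 2 point in total SPBB with a standard deviation of 3 points", with 80% power and α 0.05, is said to need 20 participants. Recruitment is set at 26 per group, 104 in all. The Background calls the evidence on HMB and functional performance contradictory and gives no expected HMB increment on the SPPB.

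**The concern.** The question concerns an increment: what HMB adds when both arms exercise. The randomised comparison that isolates it is Ex-HMB versus Ex-Plac. The only effect size that the plan can point to is a change attributed to a source on the exercise programme. Nothing in the article turns that into an expected difference between two exercising arms, and nothing explains the move from 1.5 ± 1.0 to 2 with SD 3.

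A reader will take the 80% as the trial's power for its HMB question. If that is wrong, a null result for Ex-HMB versus Ex-Plac could be read as evidence that HMB adds nothing when the trial had little chance of seeing a moderate increment. The looser wording of the aim also leaves room to rest the conclusion on Ex-HMB versus Control, which could be positive from exercise alone.

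**Working it through.** **Inputs.** From Sample size: difference δ = 2, SD σ = 3, power 80%, α 0.05 (sidedness not stated; two-sided used here), 20 participants, 26 recruited per group, benchmark 1.5 ± 1.0. Assumptions made here: HMB increments of 1.0 and 1.5 points and an SD of 2. Clustering is ignored throughout because the article gives no intracluster correlation, so the powers below are upper bounds in that respect.

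**Step 1: reproduce the 20.**
- Two groups, normal approximation: n = 2(1.96 + 0.84)²σ²/δ² = 2 × 7.85 × 9/4 = 35.3, so 36 per group (t-test: 36.3, so 37). One-sided: 28 (t-test: 29).
- One sample or paired, two-sided: (1.96 + 0.84)²σ²/δ² = 7.85 × 9/4 = 17.7; the t-test gives 19.67, so 20.

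Of these, only the one-sample or paired test returns 20. The stated 80% therefore fits a test of change within a group, not a comparison of two arms. The 26 is 20 × 1.3.

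**Step 2: power for Ex-HMB versus Ex-Plac, 20 per arm, SD 3.** The standard error is 3 × √(2/20) = 0.949. Two-sample t-test, two-sided 5%:

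| True HMB increment | Increment / SE | Power |
|---|---|---|
| 1.0 | 1.05 | 18% |
| 1.5 | 1.58 | 34% |
| 2.0 | 2.11 | 54% |

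The difference detectable with 80% power is 2.73 points. If all 26 per arm were analysed, it would be 2.38, with 42% power for 1.5 points.

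**Step 3: dependence on the SD (20 per arm).**

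| SD | Power, 1.0 | Power, 1.5 | Power, 2.0 | Detectable at 80% |
|---|---|---|---|---|
| 3 (protocol) | 18% | 34% | 54% | 2.73 |
| 2 (assumed, as baseline adjustment might give) | 34% | 64% | 87% | 1.82 |
| 1.0 (if ± 1.0 is the SD of change) | 87% | over 99% | over 99% | 0.91 |

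**Step 4: use all four arms.** In a 2x2 model the HMB effect averaged over exercise levels compares 40 with 40. At SD 3 its standard error is 3 × √(2/40) = 0.671. Power is 31% for 1.0, 60% for 1.5 and 84% for 2.0, and the detectable difference is 1.90 (1.27 at SD 2, 0.63 at SD 1.0). This estimate answers the HMB question only if the effect is similar with and without exercise. The interaction itself has standard error 3 × √(4/20) = 1.342, twice that of the pooled effect, so the data can check that condition only weakly.

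**The case against.** A reader might infer that the plan sets 2 points as the HMB target, and that HMB must therefore add more than the whole exercise effect for the trial to succeed. The documents do not support this, for three reasons.

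- Sample size never assigns the 2 points to an HMB contrast, and the arithmetic behind the 20 suggests a within-group change.
- The 1.5 is called a clinically relevant change after 12 weeks. It is not described as exercise minus control, nor as the effect at 24 weeks.
- The word must would hold only for 80% power at SD 3. The pooled contrast at SD 2 detects 1.27 points, and at SD 1.0 both contrasts detect less than 1 point.

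Two further objections have weight. First, the aim is also worded as the effect of the combination. Under that wording Ex-HMB versus Control is relevant, and an exercise-based benchmark is less out of place. Second, a missing contrast or model term may sit in the full protocol or analysis plan; calling the arms four parallel groups excludes no factorial analysis, and the planned generalized linear models could hold one. Neither the unnamed contrast nor the unmentioned 2x2 is therefore an error in itself.

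What remains concerns what is stated. The section gives an effect, an SD, a source and a power. No analysis plan can make an exercise-programme benchmark support an HMB increment, or give 20 per arm 80% power for a 2-point difference between two arms at SD 3.

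**Conclusion.** The point holds in limited form. The sample size rests on a 12-week change from the source cited for the exercise programme, is moved to 2 points with SD 3 without a reason, and carries no HMB-specific justification. The stated 80% power with 20 participants does not apply to Ex-HMB versus Ex-Plac: on the protocol's own difference and SD that contrast has 54%, and for an increment equal to the 1.5-point benchmark it has 34%. These figures assume 20 analysed per arm, a two-sided 5% t-test and independent participants. A smaller SD after baseline adjustment would improve them, and clustering would worsen them. The article fixes neither the adjusted SD nor the intracluster correlation, so a range is the honest statement.

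**What to change.** 1. In Sample size, give the between-arm power for Ex-HMB versus Ex-Plac at 1.0, 1.5 and 2.0 points over a stated range of SDs, with an explicit allowance for clustering. Do not attribute 80% power to that contrast. Say what the 1.5 ± 1.0 refers to and why 2 and 3 replace it.
2. Fit the four arms as a 2x2 with exercise, HMB and their interaction. Report the HMB effect across exercise levels beside Ex-HMB versus Ex-Plac, not in place of it, and note that the pooled estimate assumes little interaction.
3. State that Ex-HMB versus Control speaks to the combination and cannot by itself support a claim about HMB.

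The cost is wording and analysis only, with no extra participants. The downside is that the published power for the HMB question becomes less favourable, and the pooled estimate brings an assumption that the trial can test only weakly.

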### Statistical analysis

Analysis will be performed on participants who attended at least 80% the training sessions and completed all the measurements. Treatment effects will be tested using generalized linear models. All models will be adjusted for the baseline outcome value and repeated adjusting for gender, age, the group effect, and confounding factors.

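### The stated 80% power with 20 participants per group does not follow from the protocol's own inputs: two groups of 20 give about 54%, and the figure of 20 matches a paired or one-sample calculation

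*Protocol article*

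**What the plan says.** The Sample size section gives two sets of figures for SPPB, the primary outcome. The first, taken from a cited study in similar subjects, is that "a clinically relevant change is about 1.5 ± 1.0 points increments after 12-weeks". The second drives the calculation: "Differences of 2 point in total SPBB with a standard deviation of 3 points with a power of 80" (per cent), where "α of 0.05 can be estimated with 20 participants". The 20 is then raised for 30% loss to 26 per group, 104 in all. The article does not say where the 2 or the 3 comes from, whether 3 is the SD of scores or of within-person change, or what the ± 1.0 denotes.

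Study design and settings describes four parallel groups with clusters randomized, so the effect of interest is a difference between groups. Under Statistical analysis, "All models will be adjusted for the baseline outcome value".

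**The concern.** A stated difference, SD, alpha and power determine the sample size once the test is chosen. For a comparison of two independent groups, a standardized difference of 2/3 needs many more than 20 per group. If 20 came from a formula for change within one group, the 80% does not apply to the randomized comparison. A reader who took the 80% at face value would then read a null SPPB result as firmer evidence of no effect than the design can supply.

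The inputs are also unsettled. The SD of 3 is unsourced and stands next to a spread of 1.0 for change on the same instrument, with nothing to connect the two. The baseline-adjusted analysis depends on a correlation that is not given.

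**Working it through.** **Inputs.** Difference 2, SD 3, power 80%, alpha 0.05 and n = 20 per group, all from Sample size. Sidedness is not stated, so two-sided is used first. Baseline adjustment is from Statistical analysis. Clustering is ignored throughout. Power is from the noncentral t distribution unless marked otherwise.

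**1. Reproducing the 20.** For a paired or one-sample two-sided t-test with 3 as the SD of the differences, the normal formula is n = (1.960 + 0.842)² × 3²/2² = 17.7. The exact t solution is 19.67, so 20, with power 80.7%. This gives the stated figure exactly.

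**2. Two independent groups, same inputs.**
- Required n per group: 2 × (1.960 + 0.842)² × 3²/2² = 35.3, so 36 by the normal formula. The exact t solution is 36.3, so 37.
- Power at 20 per group: noncentrality (2/3) × √(20/2) = 2.108, 38 degrees of freedom, critical value 2.024. Power is 53.8% (normal approximation 55.9%).
- At 26 per group with nobody lost, power is 65.4%.

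**3. Other tests that might have been meant.**

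| Test | n per group for 80% | Power at 20 per group |
|---|---|---|
| Two groups, one-sided | 29 | 66.5% |
| Four-group ANOVA, means spanning 2 points | 26 to 51, by pattern of means | 38% to 68% |
| Factorial main effect, 40 v 40 | 18 (normal formula) | 83.8% |

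Only the factorial main effect comes near 20, and it does not give 20 exactly.

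**4. Effect of baseline adjustment, if 3 is the SD of scores.** Residual SD = 3 × √(1 − r²), where r is the baseline-to-follow-up correlation. The values of r are assumptions, because the article gives none.

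| Assumed r | Residual SD | Power at 20 per group |
|---|---|---|
| 0.5 | 2.60 | 66% |
| 0.6 | 2.40 | 73% |
| 0.7 | 2.14 | 82% |
| 0.8 | 1.80 | 93% |

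Power reaches 80% at r of about 0.68.

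**5. Effect of baseline adjustment, if 3 is the SD of change.** This is the reading under which step 1 gives 20. With equal variances at the two visits, the score SD is 3/√(2(1 − r)), so the residual SD is 3 × √((1 + r)/2). For r = 0.5, 0.6, 0.7 and 0.8 this is 2.60, 2.68, 2.77 and 2.85, and power at 20 per group is 66%, 63%, 61% and 58%. On this reading, adjustment does not restore 80% anywhere in the assumed range.

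**6. SD 3 against ± 1.0.** If both were SDs and 3 were the score SD, then 3 × √(2(1 − r)) = 1.0 requires r = 1 − 1/18 = 0.94. If 3 were the SD of change, it would be three times the other figure. Neither link is made in the text, and the ± is not defined, so this step shows only that the two figures need reconciling.

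**The case against.** The best defence is that planning on an unadjusted SD and then adjusting for baseline is ordinary and conservative, so the real power may well reach 80%. The principle is sound, and the use of an unadjusted SD is not itself an error. But it is conservative only when the sample size is correctly derived from that SD. Here SD 3 calls for 37 per group and the plan has 20, so the adjustment would have to make up the whole shortfall through an unstated correlation.

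A second defence is the factorial main effect, which would have adequate power at 20 per cell. The article describes no pooled analysis of that kind, so the stated power cannot be rested on it.

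A third is that a condensed article may leave the source of the SD to the full protocol. That is fair for the source alone, which is why it is secondary here. It does not cover the printed difference, SD, power and n, which disagree with one another for a two-group test.

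A reader might also infer that 3 is a spread of cross-sectional scores, that ± 1.0 is the proper SD, and that the plan therefore uses the wrong scale of variability. The document does not support this. Its wording allows 3 to be the SD of differences, and the exact match to a paired calculation points that way. The ± 1.0 is not labelled an SD and refers to 12 weeks, whereas the intervention lasts 24. Putting 1.0 in place of 3 would lift the computed power at 20 per group above 99.9% and hide the shortfall.

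**Conclusion.** The concern holds for the power claim. On the article's own inputs, a two-sided comparison of two groups of 20 has about 54% power rather than 80%, and 37 per group would be needed. The likeliest explanation is a paired or one-sample formula applied to a between-group question. That is inferred from the exact match to 20; the article does not say so.

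The 54% assumes a two-sided test, no baseline adjustment and independent observations. With adjustment it becomes 66% to 93% for assumed correlations of 0.5 to 0.8 if 3 is the SD of scores, and 58% to 66% over the same range if 3 is the SD of change. Any positive within-home correlation lowers all of these figures; by how much cannot be computed, because the section gives neither an intracluster correlation nor a cluster size.

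The missing source for SD 3 and the lack of any link to 1.5 ± 1.0 are real but secondary. They do not show that 3 is the wrong value.

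**What to change.** Rewrite the power statement in Sample size and keep the planned number:
- State the two-group power at 20 analysed per group as about 54% unadjusted (two-sided, difference 2, SD 3).
- Show the baseline-adjusted power as a range, with the correlation labelled as an assumption.
- Say that randomizing nursing homes lowers these figures further.
- State whether 3 is an SD of scores or of change, and give its source.
- Say what ± 1.0 denotes, and reconcile both it and the 1.5 points with the 3 and the 2 points used.

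Neither 1.0 nor a residual SD should replace 3 without a sourced correlation. Table 2 schedules SPPB at enrollment and at baseline, so the score SD can be checked before follow-up data exist. That check cannot supply the baseline-to-follow-up correlation.

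The cost is one paragraph and one recalculation, with no added participants or measurements. The protocol would then carry a lower power figure than the one now printed.

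### Twenty per group does not give 80% power for a two-group comparison on the stated inputs; unadjusted power is about 54%, before any loss from clustering

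*Protocol article*

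**What the plan says.** The Sample size section of the protocol article bases the calculation on SPPB. It plans for "Differences of 2 point in total SPBB" and continues that a "standard deviation of 3 points with a power of 80% and α of 0.05 can be estimated with 20 participants", using an R package. It then allows for 30% loss to follow-up and recruits 26 per group, 104 in total. Since 20 x 1.3 = 26, the 20 is a per-group number. The section names no test, sidedness, contrast or correlation with baseline, and does not say whether SD 3 belongs to the score or to its change.

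Study design and settings describes the trial thus: "This is a cluster randomized, placebo-controlled study with four parallel groups". Its stated purpose is the efficacy of HMB given in addition to exercise. The Statistical analysis section tests treatment effects with generalized linear models, all adjusted for the baseline value of the outcome.

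**The concern.** The question is a between-group one: does a group given HMB on top of exercise do better than a group given exercise and placebo? The variance of a difference between two independent means is twice that of a single mean with the same n and SD, so the per-group requirement is about double that of a one-group test. A figure of 20 for a standardised difference of 2/3 is too small for two groups and about right for one.

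At stake is the power claim for the primary outcome. If 20 evaluable per group does not deliver 80%, the trial could miss its own target difference much more often than the stated one time in five, and a null result for HMB would be less informative than the article implies. The Background faults earlier trials for small samples, so the figure matters to the trial's own rationale.

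**Working it through.** **Inputs (Sample size section).** Difference 2 points, SD 3, power 80%, alpha 0.05, stated n = 20 per group before loss, 26 recruited. Standardised difference d = 2/3 = 0.667. Alpha is taken as two-sided, with one-sided shown as a check.

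**1. Reproducing the stated 20.** One-sample or paired t-test, two-sided, noncentrality d x sqrt(n):
- n = 19: power 78.5%
- n = 20: noncentrality 0.667 x sqrt(20) = 2.98 on 19 df, power 80.7%

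The exact solution is 19.67, which rounds up to 20. This is the standard unadjusted calculation that returns the stated figure.

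**2. Two independent groups, unadjusted.** Normal approximation:

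n per group = 2 x (1.960 + 0.842)^2 x SD^2 / difference^2 = 2 x 7.849 x 9 / 4 = 35.3, so 36.

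The t-test solution is 36.3, so 37. One-sided, the t-test needs 28.5, so 29. None of these is near 20.

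**3. Power with the planned numbers.** Two-sided two-sample t-test, noncentrality d x sqrt(n/2):

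| Evaluable per group | Power for 2 points, SD 3 |
|---|---|
| 18 (26 x 0.7 = 18.2) | 49.3% |
| 20 | 53.8% |
| 26 (no loss) | 65.4% |

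At 20 per group the noncentrality is 0.667 x sqrt(10) = 2.11 on 38 df. One-sided power at 20 is 66.5%. The difference detectable with 80% two-sided power at 20 per group is 2.7 points.

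**4. Effect of baseline adjustment.** The article gives no correlation r, so a range is shown. If SD 3 is a raw-score SD, the residual SD is 3 x sqrt(1 - r^2):

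| r (assumed) | Residual SD | Power at 20 per group |
|---|---|---|
| 0.3 | 2.86 | 58% |
| 0.5 | 2.60 | 66% |
| 0.6 | 2.40 | 73% |
| 0.68 | 2.20 | 80% |
| 0.7 | 2.14 | 82% |

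If SD 3 is instead the SD of change, with equal variances at both visits, the residual SD is 3 x sqrt((1 + r)/2). That is 2.60 at r = 0.5 and 2.75 at r = 0.68, so a high correlation no longer rescues the figure. Reaching 2.20 would need a correlation of about 0.08, close to none.

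**5. Clustering.** Everything above treats residents as independent. The article gives no intracluster correlation or number per home, so this is illustration only: with 10 residents per home and an ICC of 0.05, the design effect is 1 + 9 x 0.05 = 1.45. Twenty per group then act like 20 / 1.45 = 13.8, and unadjusted power falls from 54% to about 39%. The requirement of 37 becomes 37 x 1.45 = 53.7, so about 54 per group.

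**The case against.** The strongest defence is that the planned model is not an unadjusted t-test. The Statistical analysis section adjusts every model for baseline, and with a raw-score SD of 3 and a correlation near 0.7, 20 per group would reach 80% among independent residents. This stands as far as it goes: 54% should not be called the power of the planned analysis. It does not rescue the stated figure, because the Sample size section neither says that SD 3 is a raw-score SD nor states a correlation, and at 0.3 to 0.6 the power is still 58% to 73%.

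A second defence is a pooled comparison of all HMB against all placebo participants: 40 against 40 gives about 84% before clustering. The article declares no such analysis, and pooling would not isolate the effect of HMB among those who exercise.

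A reader might also infer three things that the document does not support:
- That a one-sample test was in fact run. The article names a package but no test; the match at 20 is an inference. The point does not depend on it.
- That the planned effect is optimistic because 2 points exceeds the value in "a clinically relevant change is about 1.5 ± 1.0 points increments after 12-weeks". That sentence concerns a change and the planned figure a difference. The planned SD of 3 is also three times the quoted 1.0. If that 1.0 is an SD, the quoted evidence gives d = 1.5 and about 9 per group, so the plan would be the more cautious of the two. Pairing 1.5 points with SD 3 (64 per group) uses a combination the protocol never proposes.
- That 36 to 37 per group would be enough. It would not in a cluster-randomised trial, unless the intracluster correlation were zero or adjustment offset the loss.

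**Conclusion.** The point holds. On the stated inputs, 20 evaluable per group does not give 80% power for an unadjusted comparison of two groups. The requirement is 36 to 37 two-sided or 29 one-sided, and two-sided power is about 54% at 20, 49% at 18 and 65% at 26. These figures assume equal groups, SD 3 for the analysed quantity, independent residents and no baseline adjustment. Adjustment could raise them, to 80% at 20 per group if SD 3 is a raw-score SD and the correlation is about 0.68 or more. Clustering can only lower them, by an amount the article gives no figures to fix. This is a disagreement between stated inputs and a stated result for the design described, not a complaint about detail left to a fuller document. It concerns the primary outcome and should be corrected.

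**What to change.** Keep n = 104 and replace the 80% claim with a two-group calculation that:
- names the contrast it applies to, for example Ex-HMB against Ex-Plac;
- states the test and the sidedness of alpha;
- says whether SD 3 is for the score or for the change;
- states the baseline-to-follow-up correlation, if adjustment is relied on, with its source;
- reports the resulting power or detectable difference. Unadjusted and two-sided, at 20 evaluable per group, this is about 54% for 2 points, or 80% for about 2.7 points;
- labels that result as an individual-level figure and lowers it by a design effect, with the assumed ICC and number of residents per home stated.

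The cost is a rewritten paragraph and a less favourable power statement. No extra participants are required, and the design and planned model do not change.
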